**Table 2 Tab2:**
[figure not shown]
Example of a discrete choice task

#### Pretesting

The DCE survey instrument was pretested to verify the precise wording and framing of attributes and levels. The salience of efficacy figures (i.e. icon arrays) and the wording used to represent rates of adverse events was also tested for ease of comprehension. We also ascertained whether participants could manage the length of the questionnaire. Initial pretesting involved detailed face-to-face interviews of 15 patients. Secondary testing involved the administration of the pilot survey to 40 patients. Participants for pretesting were drawn from patients with end-stage OA who were waitlisted for primary TKA at SVHM. Patients were approached during their attendance at the orthopaedic preoperative assessment clinic at SVHM after consent for TKA by an orthopaedic surgeon. The main issue raised by patients was related to the timing of scenarios. The DCE task was based on possible scenarios postoperatively where patients were asked to imagine that they have had their knee replacement surgery. The detailed interviews revealed that many patients tended to relate the attributes to their current health state. Therefore, the wording of attributes was changed to reinforce the importance of post-surgery in the final design of the survey. Overall, patients felt that the DCE covered all important aspects relating to the postoperative period following knee replacement surgery.

### Standard of care

Patients will undergo surgery and postoperative care as per SVHM’s routine TKA programme which has been standardised through the use of clinical pathway protocols and validated in a RCT [28]. Postdischarge rehabilitation involves either an in-patient or a home-based physiotherapy programme which is predetermined during preadmission clinic assessment using a validated discharge predictor tool [29]. Both programmes are standardised and conducted through SVHM’s in-patient or Hospital-In-The-Home service and are followed by referral to a community-based physiotherapy programme, based on the locality of the patient’s residence. At the preadmission clinic, all patients receive an instruction booklet outlining the continuum of care for TKA. All patients are reviewed post surgery in the same clinic at intervals of 6 weeks, and 3, 6 and 12 months and annually thereafter.

### Outcome assessments

#### Data capture

Demographic information collected at baseline will include age, gender, comorbidities, body mass index and socioeconomic data.

***Primary outcomes***: will be (1) changes in patient-reported knee pain and disability between baseline and 12 months post TKA, and (2) patient satisfaction.

Pain and physical function will be measured on the WOMAC Osteoarthritis Index [27]. The WOMAC consists of 24 items covering three subscales: pain (five items), stiffness (two items) and physical function (17 items). The pain and physical function subscales will be used, each subscale transformed to a score ranging from 0 to 100, with a higher score indicating greater pain and physical function. The WOMAC is a widely used questionnaire specifically designed to evaluate knee and hip OA [30, 31]. Patient satisfaction will be derived from the Self-administered Patient Satisfaction Scale (SAPS) for primary knee arthroplasty, a validated self-administered patient satisfaction scale [30]. Patients will be mailed both questionnaires at 12 months and patients who do not attend review clinics will complete the post-TKA surveys via phone call from a study coordinator, who will be blinded to intervention allocation.

***Secondary outcomes***: will be (1) changes in patient-reported psychological wellbeing between baseline and 12 months post TKA. Psychological wellbeing will be derived from the 12-item short form version of the Veterans RAND Health Survey mental component score (VR-12) [31], (2) differences in expectations of recovery between baseline and 1 week prior to scheduled TKA for patients in the intervention arm. Recovery expectations following TKA will be measured using the 19-item Hospital for Special Surgery: Knee Surgery Expectations Survey [32]. This measure forms a part of the larger study survey, but is measured before patients complete the DCE component, (3) concordance between matched surgeon and patient expectation for recovery following TKA. Surgeons will complete the same expectation survey as patients immediately following consultation and consent for surgery. The surgeon and patient expectation survey will then be paired for analysis.

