**Methods/design:**

One hundred and thirty-two people with end-stage OA on the waiting list for TKA will be recruited and randomly allocated to one of two groups using computer-generated block randomisation. A randomised controlled trial (RCT) adhering to SPIRIT and CONSORT guidelines will evaluate the effect of administering a DCE prior to surgery on patient-reported pain and function and satisfaction following TKA. Patients in the intervention arm will complete a survey containing the DCE, compared to the control group who will complete a modified survey that does not contain the DCE activity. The DCE contains information on actual risks of postoperative complications, as well as health status after TKA. The DCE encourages patients to actively make trade-offs between risks and health outcomes to elicit their preferences. Participants in both groups will be required to complete the survey after consenting to have the procedure, but prior to surgery during their routine preadmission appointment at St. Vincent’s Hospital, Melbourne, Australia (SVHM). Patients in both the intervention and control groups will also be required to complete a brief patient expectation survey 1 week prior to scheduled TKA. In addition, orthopaedic surgeons will complete a brief expectations survey for each patient consented for TKA to compare matched surgeon and patient expectations for recovery following TKA. Primary outcomes will be evaluated by a blinded examiner at 12 months post surgery using a validated self-reported pain and physical function scale, and a validated patient satisfaction scale. Secondary outcomes will include a range of validated measures of health and psychological wellbeing. All analyses will be conducted on an intention-to-treat basis using linear regression models.

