## Methods

### Experimental design

The design is a two-arm, blinded, randomised controlled clinical trial comparing satisfaction and health outcomes of TKA patients who are provided with a DCE prior to undergoing TKA, with that of a control group. Patients in the intervention arm will complete a survey containing the DCE. Patients in the control arm will complete a survey that does not contain the DCE activity. Patients will also complete a brief patient expectation survey 1 week prior to scheduled TKA. Outcomes will be compared at 12 months after TKA. In addition, orthopaedic surgeons will complete a brief expectations survey for each patient consented for TKA. This will allow for a matched surgeon/patient comparison of expectations for recovery following TKA. The study strategy is registered, constructed and presented according to the recommendations of the Standard Protocol Items: Recommendations for Interventional Trials (SPIRIT) [25] (see Additional file 1 SPIRIT checklist) and Consolidated Standards of Reporting Trials (CONSORT) guidelines [26].

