### Timelines

This is a 1-year study with an anticipated start date of February 2016 and end date of January 2017. See Table 3 for SPIRIT schedule of study including enrolment, interventions and assessments.

**Table 3 Tab3:** SPIRIT trial study schedule

Activity/assessment	Enrolment	Randomisation	*t* _*1*_	*t* _*2*_	*t* _*3*_	*t* _*4*_
	−*t* _*1*_	0				
Baseline data, demographics	X					
Eligibility screen	X					
Informed consent	X					
Randomisation		X				
Baseline assessments battery^a^			X			
Expectation survey^b^				X		
Total knee arthroplasty					X	
12-month assessments^c^						X

^a^Baseline assessments will be given to patients during their preadmission appointments and completed with the assistance of the study coordinator. Assessment items include: Western Ontario and McMaster Universities (WOMAC) Osteoarthritis Index; Veterans RAND Health Survey mental component score (VR-12); Big Five Personality Inventory; Locus of Control; Risk Attitudes; Hospital for Special Surgery: Knee Surgery Expectations Survey; Fear Avoidance Beliefs Questionnaire; Pain Catastrophising Scale; Life Orientation Test-revised Questionnaire; and the DCE survey for patients in the intervention group

^b^Patients will complete the Hospital for Special Surgery: Knee Surgery Expectations Survey 1 week prior to scheduled TKA via phone with study coordinator

^c^12-month assessment will be given to patients at their 1-year post-TKA surgical review visit. Assessments include: WOMAC; VR-12 (this assessment is routine for all patients undergoing TKA)

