### Statistical analysis

Statistical analysis will be by intention-to-treat. Categorical variables will be analysed using chi-squared tests (or Fisher’s exact test for small samples) while continuous variables will be analysed using *t* tests (parametric) and Mann-Whitney (non-parametric) tests for symmetrically and asymmetrically distributed data, respectively. The significance of differences in dichotomous data will be tested using generalised estimating equations or a linear mixed model. If there are chance imbalances in baseline patient characteristics hypothesised to influence the main outcomes, then statistical techniques that allow adjustment for confounding variables will be used as secondary analyses. DCE data will be analysed based on extensions to logistic regression, including multinomial logit models, mixed logit models and generalised multinomial logit models [45]. If there is more than 5 % missing data, sensitivity analysis allowing for different assumptions, such as the best or worst possible scenario, will also be reported for the main outcomes of the study. Cohen’s kappa coefficient will be used to assess concordance between surgeon and patient expectations.

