It is proposed that the DCE validated in the current protocol will aid in better realigning patient expectations with those of their surgeons, which will result in improved knowledge and more realistic expectations for recovery. Better aligning patient and surgeon expectations will, therefore, likely result in improved postoperative health outcomes and satisfaction amongst patients. Reducing the rate of patient dissatisfaction commonly seen in patients following TKA will help to reduce the burden associated with poor outcomes on the health system (i.e. ongoing outpatient consultations, prolonged requirement for allied health services, etc.). Furthermore, exploring whether risk-benefit preferences are influenced by patient characteristics will provide critical information for educating surgeons to understand the anxieties faced by patients and for communicating these to patients undergoing surgery.

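### Secondary outcome 2 measures expectations as a before–after change in the DCE arm only, although both arms complete both surveys and the trial asks whether the DCE changes expectations

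*Protocol article*

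**What the plan says.** Under Outcome assessments (Data capture), the second secondary outcome is "differences in expectations of recovery between baseline and 1 week prior to scheduled TKA for patients in the intervention arm", measured with the 19-item Hospital for Special Surgery knee expectations survey. The same paragraph says the baseline measurement "is measured before patients complete the DCE component".

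The control arm supplies the same two measurements:

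- **1 week before surgery.** The Abstract (Methods/design) states: "Patients in both the intervention and control groups will also be required to complete a brief patient expectation survey". Footnote b of Table 3 (Timelines) sets no arm restriction: "Patients will complete the Hospital for Special Surgery: Knee Surgery Expectations Survey 1 week prior to scheduled TKA via phone with study coordinator".
- **Baseline.** Footnote a of Table 3 lists the expectations survey in the common baseline battery. The only item it limits to one arm comes last: "and the DCE survey for patients in the intervention group". Experimental design agrees: "Patients in the control arm will complete a survey that does not contain the DCE activity".

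The Discussion says the project uses a randomised trial to find out whether a DCE before surgery improves expectations, along with health outcomes and satisfaction. The Abstract's Background gives better expectations as the route to greater satisfaction.

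The Statistical analysis section lists generic tests for categorical and continuous variables. It names no between-arm comparison of expectations and no specific test for this outcome.

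**The concern.** Expectations are the proposed mechanism of the intervention, and this outcome is the one that tracks their change after the DCE. Confined to the intervention arm, it becomes an uncontrolled before–after comparison inside a randomised trial. Anything that moves expectations in both arms between the two surveys would be counted as a DCE effect.

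The article itself describes candidates:

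- Patients receive health assessment and education at the preadmission clinic (Participants).
- All patients receive an instruction booklet there (Standard of care).
- The baseline survey is completed electronically at that visit (Intervention), while the 1-week survey is by telephone with the coordinator (Table 3, footnote b).

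The error could run either way: a shared shift could create an apparent DCE effect or offset a real one. The control arm's change would show which, but the outcome as defined does not use it.

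**Working it through.** **1. The plan's own figure.** The article gives no sample size, SD or target difference for expectations. The number available comes from the satisfaction calculation: 77% v 51%, two-sided alpha 0.05, power 80%.

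- Mean proportion = (0.77 + 0.51)/2 = 0.64; difference d = 0.26.
- n = [1.960 × √(2 × 0.64 × 0.36) + 0.842 × √(0.77 × 0.23 + 0.51 × 0.49)]² / 0.26² = (1.330 + 0.550)² / 0.0676 ≈ 52.3, so 53 per group.
- With continuity correction: (52.3/4) × [1 + √(1 + 4/(52.3 × 0.26))]² ≈ 59.8, so 60 per group.

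The stated 60 is reproduced with the correction. Adding 10% gives 60 × 1.10 = 66 per arm, as stated. I use n = 60 below.

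**2. Within-arm test when the DCE does nothing.** Assumptions, none from the documents: a drift δ common to both arms, in SDs of the score; equal SDs at both times; test–retest correlation r; a two-sided paired test at 5% (normal approximation).

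- SD of change = √(2(1 − r)). For r = 0.6 this is √0.8 = 0.894.
- Noncentrality m = (δ / SD of change) × √60, with √60 = 7.746.
- P(significant) = Φ(m − 1.96) + Φ(−m − 1.96).

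| Common drift δ | m (r = 0.6) | P(significant), r = 0.6 | Range, r = 0.5 to 0.7 |
|---|---|---|---|
| 0 | 0 | 5% | 5% |
| 0.2 SD | 1.73 | 41% | 34–52% |
| 0.3 SD | 2.60 | 74% | 64–85% |

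If drift is expressed in SDs of the change score instead, the values at 0.2 and 0.3 are 34% and 64%. That is the r = 0.5 case, where the SD of change equals 1.

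**3. Between-arm test in the same situation.** A drift shared by both arms cancels in the difference between them, so with no DCE effect the rate stays at 5% whatever the drift.

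**4. What the between-arm comparison can detect.** At 80% power and two-sided 5%:

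- Unadjusted, 60 per arm: (1.960 + 0.842) × √(2/60) = 0.51 SD.
- Unadjusted, 66 per arm: 2.802 × √(2/66) = 0.49 SD.
- Adjusted for baseline, 60 per arm, r = 0.6 assumed: 0.51 × √(1 − 0.6²) = 0.51 × 0.8 = 0.41 SD.

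**The case against.** Several points on the other side stand.

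- **The drift is not documented.** Education, booklet and baseline survey belong to the same preadmission visit, and the article does not give their order. Education given before the survey would already be reflected in the baseline score. The change of survey mode is documented, but its effect is unknown. With no drift, the within-arm test keeps its 5% level.
- **Regression to the mean is no argument here.** A reader might add it as a cause of drift. Patients are selected on waiting-list status, end-stage disease and capacity to consent, not on expectations, so an arm's mean has no expected shift from this source.
- **No paired test is written down.** It is the natural test for the outcome as defined, but it is my assumption.
- **None of the three numbered aims in the Background is explicitly to test whether the DCE changes expectations.** The Discussion does state that purpose for the randomised trial.

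A reader might also extend the criticism to surgeon–patient concordance, because the Discussion proposes that the DCE "will aid in better realigning patient expectations with those of their surgeons" and the analysis says only that Cohen's "kappa coefficient will be used to assess concordance between surgeon and patient expectations". The documents do not support that extension. The Background and Experimental design present concordance as a matched comparison in its own right. It is neither a before–after change nor limited to one arm. Which patient survey is paired with the surgeon's, and the form of kappa, can be left to an analysis plan.

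None of this removes the core point. The arm restriction is explicit in the outcome definition, and generic mention of t tests or Mann-Whitney tests does not override it.

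**Conclusion.** The point holds for the outcome as defined. A change within the intervention arm cannot separate a DCE effect from change common to both arms, so it does not answer the question that the Discussion sets for the randomised trial.

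A reader might infer that the trial cannot show whether the DCE changes expectations. That goes too far: both arms supply both measurements, so the limit lies in the definition and not in the data.

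The 41% and 74% illustrate a general property of uncontrolled before–after tests under an assumed drift and correlation. They are not error rates established for this trial.

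This should be fixed but is not critical. It is one of three secondary outcomes, and the primary comparisons of WOMAC change and satisfaction are between arms and unaffected.

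**What to change.** Redefine secondary outcome 2 as the between-arm difference in the 1-week expectations score, adjusted for the baseline score (ANCOVA), in all randomised patients. Name this comparison in the Statistical analysis section. The change within each arm may be reported descriptively beside it.

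As an optional addition, if the sponsor wants a randomised test of realignment, the patient-minus-surgeon gap based on the patient's 1-week survey could also be compared between arms.

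The cost is about one sentence in the outcomes section and one in the analysis section. No extra patients, surveys or visits are needed.

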Not all patients undergoing TKA are at equal risk of complications. A number of patient factors can increase the risk of complications for individuals undergoing TKA, including: age and gender [14], body mass index [9, 10], ethnicity [15], psychological distress [16, 17], baseline pain and functional disability [14], comorbidity profile [9, 14] and radiographic OA severity [14]. For individuals considering TKA as a treatment option very little is known about patients’ perspectives on acceptable level of risk and how closely aligned or not this risk is with their treating clinicians’.

Although patients and clinicians share similar goals of maximising treatment benefits while minimising risk, they may have different perspectives on trade-offs among benefits and risks of treatment [18]. The acceptable level of risk tolerated by a patient depends not only on the benefits provided by the TKA (significant pain relief and improvement in joint function) but also on the seriousness and severity of the disease, the availability of other treatments and other factors such as risk of complication [19]. To date, patients’ assessments of risks and benefits of surgical interventions have not been subjected to rigourous evaluation. This is important because unrealistic patient expectations and uninformed perceptions of potential benefits, risks and limitations of surgery lead to dissatisfaction following TKA [20].

It has been shown that more than one half of patients undergoing TKA have expectations of surgery that exceed those of their surgeons; in contrast, only one quarter expect less than their surgeons [21]. Patients with higher levels of expectations than their surgeons anticipated greater improvements in activity levels and those with lower expectations anticipated a higher incidence of complications. It has also been reported that the rate of dissatisfaction amongst TKA recipients with unmet expectations is as high as 49 % compared to 6 % in those whose expectations have been met [13].

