## Discussion

The outcomes of patients following TKA are beneficial on average; however, research demonstrates that patient dissatisfaction following TKA is between 15 and 30 % [13]. One of the strongest predictors of patient dissatisfaction following TKA is unmet patient expectations [21], suggesting a misalignment between patients and surgeons during the procedural consent process. Therefore, it is important to assess patients’ preferences of acceptable risk in undergoing TKA to reduce pain or improve function, which has largely been unexplored. This project aims to use DCEs to explore patient risk-benefit preferences of surgery, and will use a RCT to determine whether applying a DCE prior to surgery improves patient expectations, health outcomes and satisfaction.

DCEs are one of the most commonly used techniques for assessing patients’ preferences in the health care domain. The current research is the first to use a DCE as an intervention to improve patients’ knowledge about the outcomes of a health care intervention. DCEs are not only a useful way to present information, but also require patients to engage through the process of making trade-offs. This may help to ensure that the information presented is more readily absorbed by patients as opposed to simply reading an information leaflet. In recent years there has been an increasing emphasis on the importance of patient involvement in medical decision-making [46–48]. These interventions can improve outcomes by aligning patient and surgeon expectations of surgery, which promotes greater patient satisfaction and increases patient compliance [49].

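### The protocol says the RCT will show whether the DCE improves patient expectations, and proposes that it realigns them with surgeons' expectations, but no stated outcome compares either between arms after the DCE

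*Protocol article*

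**What the plan says.** All places are in the Protocol article.

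- **Question for the trial (Discussion).** The RCT is to "determine whether applying a DCE prior to surgery improves patient expectations, health outcomes and satisfaction". The Discussion then proposes that the DCE "will aid in better realigning patient expectations with those of their surgeons", and expects better outcomes and satisfaction to follow from that.
- **Secondary outcome 2 (Data capture).** This is "differences in expectations of recovery between baseline and 1 week prior to scheduled TKA for patients in the intervention arm". The baseline expectation survey "is measured before patients complete the DCE component".
- **Secondary outcome 3 (Data capture).** This is "concordance between matched surgeon and patient expectation for recovery following TKA". On timing: "Surgeons will complete the same expectation survey as patients immediately following consultation and consent for surgery". On method: "The surgeon and patient expectation survey will then be paired for analysis".
- **Analysis (Statistical analysis).** Surgeon-patient concordance is assessed with Cohen's kappa. Neither arm nor time point is mentioned.
- **Data collected.** Surgeons rate every patient consented for TKA (Experimental design). The baseline battery, including the expectation survey, is given to patients generally, with the DCE added for the intervention group only (Table 3, footnote a). Both groups complete the survey 1 week before TKA (Abstract, Methods/design).

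**The concern.** The Discussion presents expectations as the step through which the DCE acts, and says the trial will determine whether the DCE improves them. A randomised trial answers that by comparing arms after the intervention. The listed outcomes do not do so. The expectation change is restricted to one arm, and the concordance outcome is a pairing whose patient time point and arm contrast are left open.

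If this stands, the trial will report satisfaction and WOMAC by arm with no randomised evidence on whether the DCE moved expectations, or moved them towards the surgeon's. A null satisfaction result would then be hard to read: the DCE may have left expectations unchanged, or changed them without effect.

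**Working it through.** **1. Order of events.**

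| Step | Surgeon rating | Patient rating | DCE given? |
|---|---|---|---|
| Surgical consent | yes, once | – | no |
| Preadmission clinic, before the DCE | – | baseline | no |
| Preadmission clinic | – | – | intervention arm only |
| 1 week before TKA | – | second rating, both arms | yes, intervention arm |

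The surgeon's rating precedes randomisation, so it is a fixed reference that allocation cannot affect.

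**2. The possible readings of secondary outcome 3.**
- Surgeon with baseline: both ratings precede the DCE. The result describes untreated concordance and carries no information on the DCE.
- Surgeon with 1-week, arms not separated: with 1:1 allocation about half the pairs are post-DCE. The result is neither a clean description nor a treatment effect.
- Surgeon with 1-week, by arm: this would address the Discussion's proposal, but the text does not state it.

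**3. Can secondary outcome 2 fill the gap?** Not as written. It has no control group, although patients in both arms receive education at the preadmission clinic (Participants) and an instruction booklet (Standard of care). A change in the intervention arm could come from either, or from time alone.

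A mean change is also a weak measure of realignment, because patients start on both sides of their surgeon. The Background reports that "more than one half of patients undergoing TKA have expectations of surgery that exceed those of their surgeons", and that one quarter expect less. Let those above have gap a and those below gap b, with shares 0.50 and 0.25, and suppose full realignment:
- mean score shift = −0.50a + 0.25b
- fall in mean absolute gap = 0.50a + 0.25b

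| Assumption | Mean shift | Fall in absolute gap | Share shown by the mean |
|---|---|---|---|
| a = b = d | −0.25d | 0.75d | 33 % |
| a = b/2 | 0 | 0.50b | 0 % |
| a = 2b | −0.75b | 1.25b | 60 % |
| 60 % above, 25 % below, a = b = d | −0.35d | 0.85d | 41 % |

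Gap sizes are not in the document, so these figures are illustrative. Their one robust message is that movements in opposite directions partly cancel in a mean.

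**4. What the planned size supports.** The protocol gives no sample size for concordance. Its 60 per group comes from satisfaction rates of 77 % and 51 %, two-sided alpha 0.05, power 80 %. The pooled two-proportion formula gives 53, and 60 with continuity correction, so the figure is reproduced; 60 × 1.10 = 66 per arm.

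For a continuous gap compared between arms, the detectable difference is (1.96 + 0.84) × √(2/n):
- n = 60: 0.51 SD
- n = 66: 0.49 SD

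| True difference | Power, 60 per arm | Power, 66 per arm |
|---|---|---|
| 0.3 SD | 38 % | 41 % |
| 0.4 SD | 59 % | 63 % |
| 0.5 SD | 78 % | 82 % |

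These ignore any gain from baseline adjustment, which depends on a correlation the document does not give.

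Comparing two kappas would generally be weaker. Assume a binary rating, 50/50 margins and SE ≈ √((1 − κ²)/n) in each arm. At 60 per arm, for 0.2 against 0.4, SE = √(0.96/60 + 0.84/60) = 0.173 and power is about 21 %. For 0.2 against 0.6 it is about 69 %.

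**The case against.** The strongest reply has four parts.

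- **Realignment with surgeons is not a listed aim.** The aims at the end of the Background are to explore trade-offs, to evaluate the DCE's effect on health outcomes and satisfaction, and to compare matched expectations. The third reads as description. The Abstract's hypothesis concerns knowledge based on actual outcome data, and the DCE levels come largely from registry data, not from surgeon ratings. This stands: a reader might infer that surgeon alignment is the trial's formal hypothesis, but the text makes it a Discussion proposal. What remains is the Discussion's statement that the RCT will determine whether the DCE improves expectations, and no stated outcome compares those between arms either.
- **The article is condensed.** The pairing time point and any split of kappa by arm may be fixed in a fuller document. This stands for secondary outcome 3 taken alone, and a reader who concludes that the arms will be pooled is reading that into silence. It does not cover secondary outcome 2, where the article fixes the contrast and restricts it to one arm.
- **The data can answer the question.** This is correct. A reader might infer that the trial cannot test realignment; that holds for the stated outcomes only.
- **A raw change score is not proposed as the alignment measure; kappa is.** Also correct, so the dilution figures are no criticism of secondary outcome 3. They bear only on whether secondary outcome 2 could substitute for a gap measure.

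**Conclusion.** The concern holds in a limited form. The Discussion attributes to the RCT a finding on patient expectations, and proposes realignment with surgeons as the route to benefit. Yet no outcome or analysis in the article compares expectations, or the surgeon-patient gap, between arms after the DCE. Secondary outcome 3 leaves the patient survey and the arm contrast open, and secondary outcome 2 excludes the control arm although that arm supplies the data.

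The primary outcomes are unaffected. No effect size for the gap is given in the document, so the consequence can be sized only as precision: about 0.5 SD detectable with 80 % power, and 38 to 41 % power at 0.3 SD. A null result on the added comparison would therefore not exclude a modest shift. Nor would a positive one show that alignment explains satisfaction; that is a mediation question needing its own analysis.

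**What to change.** 1. **Descriptive aim 3.** State that the surgeon survey is paired with the patient's pre-DCE baseline survey in all patients, with kappa as planned.
2. **DCE effect on alignment.** Add a secondary outcome: the absolute patient-minus-surgeon difference in expectation score 1 week before TKA, compared between arms and adjusted for the same difference at baseline. The linear regression named in the Abstract accommodates this. Kappa by arm can accompany it as description.
3. **Secondary outcome 2.** Remove the restriction to the intervention arm and compare 1-week expectations between arms, adjusted for baseline.
4. **Interpretation.** State that item 2 tests whether the DCE shifts alignment, not whether alignment mediates satisfaction, and give the detectable difference of about 0.5 SD.

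The cost is wording: all three surveys are already planned in both arms. The price is one extra secondary comparison of modest power, with secondary outcome 2 recast as a between-arm contrast.
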